### Aims

The aims of this study are to evaluate in a randomised controlled trial (RCT), the efficacy and cost efficacy of a therapist-delivered intervention (Conquer Fear) in reducing the impact of FCR in disease-free breast and colorectal cancer survivors with clinical levels of FCR, compared to a relaxation training control intervention. Secondary aims are to evaluate patient satisfaction with the program and the relative cost-effectiveness of Conquer Fear and the relaxation interventions. Specific hypotheses are that:

1. Participants in the Conquer Fear intervention will have lower scores on the Fear of Cancer Recurrence Inventory of at least 14.5 (0.5 standard deviation) as compared to the attention control group (who receive relaxation therapy) at follow-up;

2. Participants in Conquer Fear will have less cancer specific distress, less anxiety and depression, better quality of life, fewer unmet needs, and less maladaptive metacognitions when compared to the control group;

3. Patients receiving Conquer Fear will find the therapy program useful for treating their FCR and be satisfied with the program; and

4. The Conquer Fear intervention will be cost-effective compared to the relaxation comparator intervention.

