### Outcomes

All participant outcomes are assessed using either an online or paper and pencil self-report questionnaire containing the measures listed below. Participants are posted or e-mailed, as preferred, the questionnaires, to be completed and returned in a reply-paid envelope or online. Questionnaires are completed upon enrollment in the study prior to randomisation, immediately after treatment completion, 3 and 6 months after treatment completion. The researchers follow up participants who do not return their questionnaire within two weeks, with up to three phone calls at different times of the day according to a pro forma. If phone contact cannot be made, email and text reminders are sent where possible. Finally, a replacement questionnaire is sent 3 weeks after the non-returned questionnaire.

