#### Exploratory outcomes

•Metacognitions (the cognitive processes, strategies, and knowledge that are involved in the regulation and appraisal of thinking itself.’[52]) are measured with the Metacognitions Questionnaire-30 [52,53], a 30 item questionnaire with 5 subscales measuring: cognitive confidence; positive beliefs about worry; cognitive self-consciousness; uncontrollability and danger; and need to control thoughts.

•Fear of cancer recurrence will also be measured using the Concerns About Recurrence Questionnaire (CAR-Q), a 5 item purpose designed questionnaire developed by BT and PB, to act as a brief screen of FCR. This is to test the psychometric properties of the CAR-Q.

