#### Statistical analysis

Analyses will be by intention-to-treat. Linear mixed models will be used to account for the hierarchical, non-independent nature of the data: repeated measures on patients nested within therapist. A saturated time x treatment model with unstructured covariance structure will be used to guard against misspecification of the model. Random effects of patient and therapist will be used. The primary analysis will be the comparison at the each of the 3 post-baseline (post-treatment) time points of the two arms using a contrast within this mixed model. Overall pattern of change will be assessed by testing the treatment by time interaction. Adjusted analysis, including using baseline FCRI, sex, age, time since diagnosis, cancer type, perceived risk, treatment expectancy and therapeutic alliance will also be investigated. Variables will be included in the model if they have a Kendall’s Tau correlation higher than 0.1 with FCRI. Mixed models yield unbiased estimates for data which are missing completely at random and at random [62], however, if the amount of missing data for the primary outcome is greater than 20%, sensitivity analyses will be performed by multiply imputing the missing data, and adding and subtracting clinically plausible amounts from the imputed values. These new datasets will be re-analysed, to see how conclusions change.

Secondary outcomes (QoL, distress, unmet information needs) will be analysed in a similar way to the primary outcome. Treatment satisfaction and therapist training evaluation will be described with descriptive statistics. To see if colorectal and breast cancer patients responded differently to the treatment, we will test the interaction cancer type x treatment x time. Predictors of FCR, distress and QoL at baseline will be explored using multiple linear regression. The relationship between Metacognition and FCR will examined using 1) regression to see if there is a relationship at baseline in the entire sample and then 2) using mediation techniques following the methods of Baron and Kenny [63] in the treatment group only, immediately post baseline (time 1). The CAR-Q will be compared with the FCRI using psychometric techniques.

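### The mediation analysis of metacognitions is confined to the treatment arm at one time point, so it cannot show that Conquer Fear works through metacognitions

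*Protocol article*

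**What the plan says.** The Statistical analysis section of the protocol article sets two analyses of metacognitions. The first is a "regression to see if there is a relationship at baseline in the entire sample". The second is to proceed "using mediation techniques following the methods of Baron and Kenny", and is restricted to participants "in the treatment group only, immediately post baseline (time 1"). Method, population and time point are all stated. The exposure is not named.

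Three other places bear on the point:

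- **Aims, hypothesis 2** predicts, for Conquer Fear, "fewer unmet needs, and less maladaptive metacognitions when compared to the control group". This is a between-arm claim.
- **Exploratory outcomes** places metacognitions there; they "are measured with the Metacognitions Questionnaire-30 [52,53], a 30 item questionnaire with 5 subscales".
- **Statistical analysis**, on outcomes other than the FCRI: "Secondary outcomes (QoL, distress, unmet information needs) will be analysed in a similar way to the primary outcome". Metacognitions are not in the parenthesis.

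The Outcomes section gives one schedule for all participants: "Questionnaires are completed upon enrollment in the study prior to randomisation, immediately after treatment completion, 3 and 6 months after treatment completion".

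**The concern.** A mediation analysis in a randomised trial asks whether treatment changes the mediator and whether that change carries part of the effect on the outcome. It needs a contrast in treatment. Restricting the analysis to the treated arm removes that contrast. Taking mediator and outcome at the same visit also leaves their order open.

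This matters because the article builds the intervention on metacognitive therapy and presents its theoretical basis as part of the trial's contribution. A within-arm association between the MCQ-30 and the FCRI could be reported as evidence of mechanism when it carries no information about what treatment did.

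A smaller matter sits alongside. A numbered hypothesis predicts a difference between arms in metacognitions, but neither metacognition analysis that the article describes compares the arms.

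**Working it through.** **1. What can be estimated in one arm.** Write X for arm, M for MCQ-30 and Y for FCRI. The usual regression steps are:

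- M = i1 + a·X (treatment to mediator)
- Y = i2 + c·X (total effect)
- Y = i3 + c'·X + b·M (direct effect c', mediator path b)
- indirect effect = a·b

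In the treatment arm X = 1 for everyone. The columns for the intercept and X are identical, so the design matrix [1, X] has rank 1 instead of 2. Hence a, c, c' and a·b cannot be estimated. Only b, the slope of FCRI on MCQ-30 among treated patients, is left.

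**2. The pre-to-post reading.** No exposure is named, so one could take time (baseline to post-treatment, within the treated) as the exposure. That analysis can be run but is uncontrolled. Patients enter on an FCRI severity score of 13 or more, so some fall on retest is expected without any treatment. The Relaxation training section says that the control arm is there to account for therapist contact and other non-specific effects. Leaving it out discards that protection.

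**3. Numbers available.** The Sample size section gives 260 patients, 20 therapists, 30% dropout, ICC 0.01, a difference of 14.5 and SD 29.

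- Plan's own figure: 85 per arm for 90% power. Completers per therapist are 13 × 0.7 = 9.1, so the design effect is 1 + 8.1 × 0.01 = 1.081. Total = 2 × 85 × 1.081 / 0.7 = 262.5, or 13.1 per therapist. This agrees with 13 per therapist and 260 to within rounding.
- Completers per arm, assuming 1:1 allocation: 130 × 0.7 = 91.

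**4. Illustration of the within-arm association.** Power to find a correlation r with n = 91, by Fisher's z, is Φ(atanh(r)·√88 − 1.96), where √88 = 9.381. The correlations are assumed; the article gives none.

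| r (assumed) | atanh(r) × 9.381 | Power |
|---|---|---|
| 0.3 | 2.90 | 83% |
| 0.4 | 3.97 | 98% |
| 0.5 | 5.15 | 99.9% |

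The effect of treatment on metacognitions does not enter the formula.

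**5. Simulation under assumed paths** (4000 runs, 91 per arm, standardised variables, clustering ignored). The two-arm test calls mediation when paths a and b are both significant.

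| Assumed truth | Treated-only slope significant | Two-arm test significant |
|---|---|---|
| a = −0.5, b = 0.5 | 99.5% | 91.4% |
| a = 0, b = 0.5 | 99.3% | 5.4% |
| a = 0, b = 0, shared cause (loading 0.6) | 85.2% | 4.8% |
| a = −0.5, b = 0, shared cause (loading 0.6) | 85.4% | 90.6% |

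Rows 1 and 2 show that the treated-only slope does not distinguish a treatment that moves metacognitions from one that does not; the two-arm test does. Row 4 shows the limit of using both arms: if treatment moves the mediator and an unmeasured cause links mediator and outcome, the two-arm test is still misled. Hence the need for baseline adjustment, a later outcome and a sensitivity analysis.

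**6. Hypothesis 2.** After dropout and design effect, 91 / 1.081 = 84.2 effective patients per arm remain. Power for a 0.5 SD difference is Φ(0.5 × √(84.2/2) − 1.96) = Φ(1.28), about 90%. If MCQ-30 clusters as assumed for the FCRI, a between-arm comparison is as well powered as those for the secondary outcomes.

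**The case against.** The strongest case on the other side has four parts.

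- **The mechanism would not be supported automatically.** A reader might infer that the planned analysis would confirm the theory even if Conquer Fear changed nothing. The document does not support that. The steps require a demonstrated path from exposure to mediator. With arm as exposure they cannot be completed; with time as exposure that path would be null if metacognitions did not change. This stands, and the percentages above describe only the association that is left over.
- **The illustration is assumed.** Correlations of 0.3 to 0.5 are not in the article, and 91 completers uses a dropout that the sponsor expects not to reach. This also stands.
- **Hypothesis 2 may be analysed elsewhere.** A reader might infer that part of it goes untested. Only a condensed article is available. The omitted measure is labelled exploratory, the list is of secondary outcomes, and a full analysis plan could supply the model. What is left is an internal mismatch between a numbered between-arm hypothesis and its label and place in the analysis.
- **The aim is minor.** No hypothesis claims mediation, and the text frames this step as examining a relationship. That limits the weight of the point. It does not rescue the choice, since a named mediation method is fixed to a population in which it cannot estimate a treatment effect.

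The restriction to one arm at one time is stated outright, so the brevity of an article does not explain it.

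**Conclusion.** The concern holds for the mediation analysis. As specified, it cannot estimate an indirect effect of randomised treatment, and no result from it could show that Conquer Fear works through metacognitions. This follows from arm being constant and needs no assumed figure. The 83% to 99.9% range is an illustration under assumed correlations of 0.3 to 0.5 and 91 completers, and should be cited only as such.

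A reader might conclude that the trial cannot answer either question about metacognitions. That is not so: the questionnaires cover all participants at baseline and three later times, so the limitation lies in the stated analysis and not in the data.

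On hypothesis 2 the finding is an inconsistency to reconcile. The primary analysis, sample size and efficacy conclusion are untouched. The change should be made before unblinding but is not critical to the trial.

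**What to change.** 1. **Mediation.** Replace the treatment-only analysis with one in both arms. Use randomised arm as exposure, MCQ-30 from the questionnaire at the end of treatment as mediator, and FCRI at one later time (3 or 6 months, named in advance) as outcome. Adjust for baseline MCQ-30 and baseline FCRI, and keep therapist in the models. Report the indirect effect as the product of the two paths with a bootstrap interval, and add a sensitivity analysis for mediator-outcome confounding, which randomisation does not remove.
2. **Hypothesis 2.** Add MCQ-30 to the mixed model used for the secondary outcomes, and give metacognitions the same status in the Aims, the outcome lists and the analysis section.
3. **Time label.** Reconcile time 1, described as directly after baseline, with a schedule whose first follow-up comes at the end of treatment.

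Cost: a change of wording and modest extra analysis. No new data are needed. Using a later FCRI may lose some further participants to dropout, which should be handled as for the primary outcome.

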## Discussion

### Theoretical significance

This RCT advances the field by representing the first controlled trial of a novel, evidence-based and theoretically-based model of psychological support for cancer survivors with high FCR. Further, the inclusion of a health economic evaluation will strengthen the study further. Given the dearth of intervention research anchored in theoretical frameworks, this trial is an important next step in filling the gap in knowledge about how best to support this large and growing group. Extensive preliminary research and pilot work has demonstrated the likely success of this model.

### Clinical significance

The Conquer Fear intervention aligns with emerging priorities in survivorship care in cancer which identify promotion of quality of life and maximizing well-being and optimal participation in social and occupational roles as central to care, rather than the traditional surveillance-based approach to follow-up which focuses on identification of new disease or late complications of cancer treatment. It is also in line with consumer priorities for survivorship research [64]. This intervention has the potential to reduce FCR and improve the QoL of patients, and reduce health care costs. The eventual goal of this study is to distribute an evidence-based, manualised, psychological intervention for FCR. Implementation of the Conquer Fear intervention will therefore help to eradicate barriers to appropriate psycho-social care for survivors, and has far-reaching service and policy implications in terms of implementing ‘best practice’ recommendations for the ever-increasing numbers of cancer survivors.

## Abbreviations

FCR: Fear of cancer recurrence; RCT: Randomised controlled trial; FCRI: Fear of cancer recurrence inventory; CAR-Q: Concerns About Recurrence Questionnaire; S-REF: Self-Regulation of Executive Function; ATT: Attentional training technique; PMR: Progressive muscle relation; CTS_R: Revised cognitive therapy scale; QALY: Quality-adjusted-life year; WAI-SR: Working Alliance Inventory short-form revised; AR-DRG: Australian Refined Diagnosis Related Groups; ICC: Intra-cluster correlation
